#### Cost data

Supplemental cost data will be collected from two participating hospitals to illustrate costs during the study period, although we will not use these data in the main analysis. Medical costs will be gathered using individual receipt data from the two hospitals. To gather the cost data of medical services used in medical institutions other than the two hospitals and social services, we will assess the number of such services used through the Japanese version of the Client Service Receipt Inventory (CSRI-J) [55]. The CRSI-J includes the cost of social security and other public or social allowances in addition to information about services. At each assessment point, staff members at the two hospitals will interview the participants about their service utilization using CSRI-J. The costs of services will be computed in reference to a previous Japanese cost study [56]. Specifically, medical service and social service costs will be calculated based on the unit costs in the National Health Insurance or the Services and Supports for Persons with Disabilities Act, respectively. In addition, the costs per hour of services from public sectors (e.g., city offices, local government, and public unemployment offices) will be estimated based on the average salaries earned by public officers of the average age in Japan.

### Sample size consideration

Based on the primary aim of this study, the sample size was calculated using the effect size reported by a previous study. That study reported an association between readmission and QoL scores (*d* = 0.26) [20] and indicated the readmission rate in Japanese psychiatric hospitals (40%, ratio of approximately 1 vs 1.5) [38]. In addition, the calculation was based on a power of 70% at a two-sided significance level of 5%. Based on these values, 430 participants will be needed. Assuming that 20% of the participants will not be discharged within 12 months and a 25% attrition rate [57], the final number of participants required was estimated to be 624. This calculation was conducted using Stata version 15.

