**Methods:**

This multicenter prospective cohort study is being conducted in 21 participating Japanese hospitals, with a target sample of approximately 600 participants admitted to the acute psychiatric ward. The study has four planned assessment points: time of index admission (T1), time of discharge (from the index admission) (T2), 6 months after discharge from the index admission (T3), and 12 months after discharge from the index admission (T4). Participants will complete self-reported measures including a QoL scale, a subjective disability scale, and an empowerment- and self-agency-related scale at each assessment point; additionally, service satisfaction, subjective view of need for services, and subjective relationships with family members will be assessed at T2 and T3. We will assess the participants’ hospitalization during the study period and evaluate several potential individual- and service-level factors associated with readmission and patient-reported experiences and outcomes. Multivariate analyses will be conducted to identify potential associations between readmission and patient-reported experiences and outcomes.

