### Procedures for data collection

After informed consent is obtained, participants will complete a self-administered questionnaire at the time of admission (T1). The staff members will assist by reading the questionnaire if necessary. Trained staff members will also complete the first assessment sheet, which includes sociodemographic information and past medical history, based on medical records. In addition, they will assess staff-rated measures based on observation and a brief interview with the participant. At discharge (T2), the participant will complete the self-administered questionnaire again. Next, staff members will complete staff-rated measures and will document the types of inpatient care that were provided during hospitalization on the second assessment sheet, based on medical records. At 6 months (T3) and 12 months (T4) after the index admission, the participant will complete a self-administered questionnaire, and staff members will complete an assessment sheet detailing staff-rated measures, readmission, and outpatient services. To prevent loss to follow-up at 6 months (T3) and 12 months (T4), staff members in the inpatient care department, outpatient care department, and outreach team will cooperate to share information on each participant’s status.

For participants who are not discharged within 12 months of the index admission, the same procedure used for the discharge survey (T2) will be conducted when the hospital stay reaches 365 days. At this time, the patient’s survey will be concluded. The main analysis will only include participants who are discharged within 12 months.

Data monitoring and management will be conducted by the Department of Community Mental Health and Law, National Center of Neurology and Psychiatry, which is independent from the grant funder. At least two researchers or research assistants will check the data to maintain data quality.

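### The enrolment target of 624 adds the loss rates to 430 instead of dividing by the fraction retained, and 430 itself belongs to 75% power, not the stated 70%; the two errors nearly cancel

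*Protocol article*

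**What the plan says.** The section Sample size consideration takes a standardised difference of d = 0.26 in QoL between readmitted and non-readmitted patients from a previous study. It adds a Japanese readmission rate given as "40%, ratio of approximately 1 vs 1.5", 70% power and a two-sided 5% level. It concludes: "Based on these values, 430 participants will be needed". It then inflates: "Assuming that 20% of the participants will not be discharged within 12 months and a 25% attrition rate", after which "the final number of participants required was estimated to be 624". No inflation formula is given.

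On who counts as analysable, Procedures for data collection states: "The main analysis will only include participants who are discharged within 12 months". Under Data analysis, Primary objectives, the models keep only participants who have both the QoL score at discharge and the 12-month readmission outcome. The abstract describes the study as one "with a target sample of approximately 600 participants admitted to the acute psychiatric ward".

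**The concern.** A loss rate is a share of those enrolled. To end with a required number, that number must be divided by the fraction expected to remain. Adding the rates to 1 and multiplying gives too small a target, and the gap widens as the losses grow. Here the losses are large, and both bear on the primary analysis: non-discharged patients are excluded by rule, and patients without the outcome are excluded by the complete-case restriction.

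At stake is whether the stated enrolment supplies the number the protocol says its primary objective needs. Readers will use 430, 624 and 70% to judge whether the study was large enough, so these three figures should be consistent with one another.

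**Working it through.** **Inputs** (all from Sample size consideration): d = 0.26; split 1:1.5 (40% readmitted); two-sided 5%; power 70%; base number 430; losses 20% and 25%; target 624.

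**1. Reproducing 624.**
- 430 x (1 + 0.20 + 0.25) = 430 x 1.45 = 623.5, rounded up to 624. This matches exactly.
- 430 x 1.20 x 1.25 = 645. No match.
- 430 / (0.80 x 0.75) = 716.7, so 717. No match.
- 430 / 0.55 = 781.8, so 782. No match.

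**2. Running 624 forward.**
- Losses in sequence: 624 x 0.80 = 499 discharged; 499.2 x 0.75 = 374 analysable. Shortfall 430 - 374 = 56, and 56/430 = 13%.
- Losses additive, both as shares of all enrolled and without overlap: 624 x 0.55 = 343.
- With 600 enrolled, in sequence: 600 x 0.60 = 360.

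**3. Checking the base number.** For two means with the larger group 1.5 times the smaller, the smaller group is n1 = (1 + 1/1.5) x (z_alpha + z_beta)^2 / d^2.
- 70% power: 1.6667 x (1.960 + 0.524)^2 / 0.0676 = 152.2, so 153; the larger group is 230; total 383.
- 75% power: 1.6667 x (1.960 + 0.674)^2 / 0.0676 = 171.1, so 172; the larger group is 258; total 430.

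The noncentral t calculation gives the same totals, 383 and 430. So 430 matches 75% power exactly and does not match the stated 70%.

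**4. Crude power at d = 0.26, 40:60 split, two-sided 5%** (noncentral t; the normal approximation agrees to within 0.3 percentage points).

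| Analysable patients | How reached | Power |
|---|---|---|
| 430 | stated need | 75% |
| 383 | need at 70% power | 70% |
| 374 | 624 enrolled, losses in sequence | 69% |
| 360 | 600 enrolled, losses in sequence | 67% |
| 343 | 624 enrolled, losses additive | 65% |

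**5. Enrolment by division.** For 70% power: 383 / 0.60 = 638.3, so 639. For 430 analysable: 430 / 0.60 = 716.7, so 717.

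**The case against.** The strongest reply is that little is lost. The protocol claims 70% power, not 75%. Against the 383 patients that 70% requires, 374 is 9 short (about 2%), and power is about 69%. This stands, and it limits the severity. A reader might infer from the 13% shortfall that the study is materially underpowered against its own plan, with power falling from 75% to 69%. The document does not support that, because it never claims 75%.

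A second reply concerns what the 25% covers. The article gives neither its denominator nor which data it removes. The primary analysis needs only QoL at discharge and readmission. Readmission is recorded by staff, with information drawn primarily from medical records, so a patient who skips a follow-up questionnaire may still be analysable. That is fair: 374 is conditional, and if attrition removed nobody from the primary analysis, up to 499 would remain. Likewise, if the 20% lay wholly inside the 25%, 624 x 0.75 = 468 would remain. But the paragraph lists the two losses separately, and the 1.45 multiplier counts both in full. Its own calculation therefore treats them as distinct losses from the required number.

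Two further inferences should be set aside. The abstract's figure of about 600 does not contradict 624; it is an approximate figure within 4% of it. And any power lost to covariate adjustment is a separate matter that would arise with 430 patients too.

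None of this rescues the calculation. The near-agreement with 70% comes from two errors in opposite directions, and the article still says that 430 are needed and that 624 enrolled will supply them.

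**Conclusion.** Wrong as written; moderate severity. The inflation step adds loss rates where it should divide by the retained fraction, and the base number does not match the stated power. On the natural reading of the losses, 624 enrolled leaves about 374 analysable patients, 56 (13%) below the stated 430; 343 remain if the losses are additive. Because 430 overstates what 70% power requires by 47 patients (430 - 383), the effect on the stated power is small: about 69% at 374, about 67% at 360 if 600 enrol, and about 65% at 343.

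These figures assume d = 0.26, a 40:60 split, and a crude two-group comparison, which is what the stated inputs describe. The analysable counts of 374 and 360 also assume that the 25% applies to discharged patients and takes them out of the primary analysis.

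**What to change.** Keep enrolment unchanged and correct the paragraph in Sample size consideration:

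- State that d = 0.26, a 1:1.5 split and a two-sided 5% level require about 383 analysable patients for 70% power, and that 430 corresponds to 75%.
- State that dividing by 0.80 x 0.75 gives about 639 enrolled for 70% power, or 717 for 430 analysable.
- State that the planned 624 is expected to leave about 374 analysable patients, with about 69% crude power.
- Say in one clause what the 25% attrition applies to, since the 374 depends on it.

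The base number and the inflation should be corrected together. Changing only the formula would give 717 from 430 and contradict the enrolment being kept. Changing only the base number would leave the additive error in place.

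The cost is a rewritten paragraph and a slightly less favourable stated figure. No extra patients are needed, and neither the analysis set nor the model changes.

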### Data analysis

#### Descriptive statistics

Descriptive summary statistics will be calculated for sociodemographic characteristics, outcomes, and other exposures. These values will be presented as means, standard deviations, medians, interquartile ranges, frequencies, and proportions, as appropriate.

#### Primary objectives

For the primary objective, mixed-effects logistic regression will be performed to assess the relationship between the QoL score at discharge (T2) and readmission over a 12-month follow-up period beginning at discharge after the index admission. In the first model, we will adjust for sex, age, and diagnosis. Next, we will conduct an analysis that adjusts for the potential covariates suggested in previous studies, for example, function (PSP score), symptoms, accommodation, problematic behaviors, past hospitalization, comorbidities, and utilization of outreach services after discharge, in addition to sex, age, and diagnosis. Statistical significance will be set at 5% (two-tailed). In these models, we will only include participants with data for both the primary exposure (QoL score at discharge, T2) and the primary outcome (readmission over 12 months).

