## Background

Over the past 50 years, there have been two predominant themes in psychiatric care worldwide, namely, community living and personal recovery for people with mental illness, which focus on the individual processes through which people with mental illness subjectively achieve meaningful lives [1, 2]. With regard to community living, as the number of patients who live in the community has increased through deinstitutionalization in developed countries [3–5], several studies have examined factors associated with readmission, which has a negative impact on sustainable community living for people with mental illness [6–16]. Previous relevant studies and systematic reviews have confirmed several individual- and service-level factors associated with readmission [6–16]. Individual-level factors include diagnosis, sex, age, treatment adherence, symptoms, housing problems, problematic behaviors, past hospitalization, and comorbidities. Service-level factors include inpatient care programs, medications, provision of care after discharge, other types of comprehensive community care and locations of hospitals and patients [11–16]. In addition, a recent study that sought to identify the various risks for readmission developed and validated a comprehensive index called the READMIT, whose score was associated with future readmission among psychiatric inpatients [17].

While several objective factors at patient discharge have been reported to be risks for future readmission, patients’ subjective experiences may also be associated with readmission. If patients’ subjective views of themselves at discharge or their experiences during hospitalization can be shown to be independent risk factors for their future readmission, psychiatric care should focus on improving these factors. Indeed, patient-reported assessments of QoL and personal recovery have been somewhat correlated with symptoms and functions [18, 19]. In addition, one recent study reported a potential association between subjective QoL and future readmission among patients with schizophrenia in Israel [20]. However, a systematic review also noted that few studies have examined the association between subjective patient views and readmission [11]. Therefore, the relationship between these variables is still hypothetical.

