## Aims and objectives

To address the evidence gap, we initiated the ePOP-J study (early discharge and Prognostic community Outcomes for Psychiatric inpatients in Japan: a longitudinal study), which is a multicenter prospective cohort study designed to investigate multiple factors, including patient-reported measures, associated with readmission and community living, in acute psychiatric patients in Japan. The overarching aim of the present study is to explore the association between patient-reported experiences and outcomes and the incidence of readmission during 12 months of follow-up. In this study, patient-reported measures, particularly QoL, will be used to assess both exposures and outcomes. The study primarily aims to evaluate the following associations and factors, although we will also perform a comprehensive exploratory analysis to identify other (non-patient-reported) factors for readmission after evaluating the described associations and factors:The relationship between readmission during the 12-month follow-up beginning at discharge after the index admission (primary outcome), and the QoL score at discharge (primary exposure).The association between readmission during the 12-month follow-up beginning at discharge after the index admission and the self-reported disability score, empowerment/self-agency-related measure score or inpatient care service satisfaction score at discharge.Influence of readmission on changes in scores for patient-reported outcome measures (QoL, self-reported disability and empowerment/self-agency-related outcome) during the study period.Other potential factors influencing score changes in patient-reported outcome measures, such as age, sex, diagnosis, length of hospital stay, living conditions, and utilization of outreach services after discharge.

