#### Patient-reported measures

The study assesses three patient-reported experience and outcome measures at all time points. The EuroQOL Five Dimensions and Five Levels (EQ-5D-5L) will be used as the primary measure of interest (primary exposure) corresponding to the primary aim of this study. The EQ-5D has been widely used in the area of mental health [42]. In addition, the scoring and language of the EQ-5D-5L have been validated in multiple countries, including Japan [43–45]. The Sheehan Disability Scale (SDS), which is a self-reported disability measure, is used to assess participants’ self-perceptions of problems in their lives. It consists of three items: work/academic activities, social activities, and family communication. Previous studies have confirmed that the Japanese version of the SDS has convergent validity with the Global Assessment of Functioning, good internal consistency, and extremely high test–retest reliability [46–48]. We will also employ a new scale to measure subjective views of empowerment and self-agency in people with mental illness. This scale asks participants whether they express themselves in their daily lives and whether they make decisions about the things that they encounter in their lives. The scale was tested in an assertive community treatment sample with relatively severe mental illness in Japan. Good factor validity has been confirmed [49]. Trained staff members help participants read and understand the sentences in each scale if necessary.

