#### Additional objectives

We will also create mixed models with repeated measures to explore the impacts of readmission on changes in QoL, empowerment/self-agency-related measure, and self-reported disability. In this model, we will adjust for sex, age, diagnosis, baseline score at admission (T1) and present psychiatric status at admission (T1). In addition, we will explore other potential factors that influence the changes in patient-reported outcomes using mixed models with repeated measures. In this analysis, we will include at least the following variables: function (PSP score), length of hospital stay, living condition, and utilization of outreach services after discharge. Because the mixed-model method can accommodate missing data, we will use the data from patient-reported measures completed at least twice at the three follow-up assessments (T2–T4), in addition to the assessment at admission (T1).

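### The readmission models do not name the admission score of the same scale, so they cannot show whether quality of life at discharge adds anything beyond quality of life at admission

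*Protocol article*

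**What the plan says.** Aims and objectives sets the primary question as the relationship between 12-month readmission and "the QoL score at discharge (primary exposure"). Under Primary objectives, mixed-effects logistic regression is fitted twice. For the first fit, "In the first model, we will adjust for sex, age, and diagnosis". The second "adjusts for the potential covariates suggested in previous studies, for example, function (PSP score), symptoms, accommodation, problematic behaviors, past hospitalization, comorbidities" and use of outreach services. Secondary objectives repeats this for self-reported disability, empowerment/self-agency and satisfaction with inpatient care.

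The admission scores exist. Patient-reported measures states: "The study assesses three patient-reported experience and outcome measures at all time points", and Table 1 marks EQ-5D-5L, SDS-J and the empowerment scale at T1. Satisfaction is first measured at T2, so it has no admission score. In Additional objectives, where the patient-reported score is the outcome, "we will adjust for sex, age, diagnosis, baseline score at admission (T1) and present psychiatric status at admission (T1").

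On use of the result, the Background says that if patients' views at discharge or experiences in hospital prove to be "independent risk factors for their future readmission, psychiatric care should focus on improving these factors". The Discussion makes a similar conditional statement about routine clinical practice, and also says that observational data cannot establish what a particular intervention does.

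**The concern.** The T1 score of the same scale precedes the exposure and is likely to correlate with it. It may also carry long-standing disadvantage that itself raises the risk of readmission. If so, part or all of the T2 association could reflect quality of life that the patient brought into hospital.

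For predicting who will be readmitted, that origin does not matter. For calling the discharge score an independent factor that care could improve, it does: the relevant question is then whether two patients who started at the same level but left at different levels have different risks. No model under Primary or Secondary objectives answers that.

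The wording of the second model's list ("for example" type, not exhaustive) leaves room for T1 quality of life. But its selection rule is what earlier studies suggested, and the Background itself says that few studies have examined patients' subjective views and readmission, so the rule is unlikely to bring the T1 score in.

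**Working it through.** **Plan's own figure.** Sample size consideration gives d = 0.26, 40% readmitted (ratio 1:1.5), two-sided 5%, 70% power and N = 430. The standard two-mean formula with these inputs gives 153 + 230 = 383 at 70% power; 430 (172 + 258) is the result at 75%. This is a separate matter and does not decide the present point, but it sets the reference: 430 analysable patients give about 75% power without T1 adjustment.

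**Inputs assumed.** The article gives no T1-T2 correlation (ρ) and no T1-readmission effect (d1). I take ρ = 0.3, 0.5 and 0.7, and several values of d1. T1 and T2 are treated as normal with equal variance in both outcome groups, so that the log-odds ratio per SD equals d. The unadjusted T2 effect is d2 = 0.26, an odds ratio of exp(0.26) = 1.30 per SD.

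**Formulas.**
- T2 effect adjusted for T1: (d2 − ρ·d1)/(1 − ρ²)
- Variance inflation for T2: 1/(1 − ρ²)
- Power: Φ(effect × √(430 × 0.24 × (1 − ρ²)) − 1.96), with 0.24 = 0.4 × 0.6. At ρ = 0: 0.26 × √103.2 = 2.64, power 75%.

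**Adjusted T2 log-odds per SD (power at N = 430).**

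| Assumed T1 effect d1 | ρ = 0.3 | ρ = 0.5 | ρ = 0.7 |
|---|---|---|---|
| ρ × 0.26 (T1 adds nothing given T2) | 0.26 (71%) | 0.26 (63%) | 0.26 (47%) |
| 0.13 | 0.24 (65%) | 0.26 (63%) | 0.33 (67%) |
| 0.26 (same as T2) | 0.20 (49%) | 0.17 (33%) | 0.15 (20%) |
| 0.26/ρ = 0.87, 0.52, 0.37 (T1 explains everything) | 0 | 0 | 0 |

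Example, d1 = 0.13 and ρ = 0.7: (0.26 − 0.091)/(1 − 0.49) = 0.169/0.51 = 0.33.

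**Association with no T2 effect at all.** If readmission depended only on T1, with an assumed log-odds of 0.4 per SD, a model with T2 alone would show about ρ × 0.4 = 0.12, 0.20 or 0.28. Adding T1 would bring it to about zero. The 0.4 is illustrative and exceeds the planned 0.26.

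**Precision.** Variance inflation is 1/0.91 = 1.10, 1/0.75 = 1.33 and 1/0.51 = 1.96. The square roots are 1.05, 1.15 and 1.40, so the T2 standard error rises by about 5%, 15% or 40%.

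**The case against.** The strongest reply is that the stated aim concerns the level at discharge. A low discharge score is low whatever its origin, and adding T1 changes the question. This stands: the planned models are correct for that aim, and a reader who infers that the primary analysis is invalid or biased for its own question goes further than the article allows.

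Other parts also stand:
- A reader might infer that the article tells inpatient care to raise quality of life. The Background speaks of psychiatric care and only on condition of an independent association; the Discussion speaks of routine practice, after covariate adjustment, and limits the causal reading.
- Adjustment for the T1 score in Additional objectives is not an inconsistency. There the scale is the outcome and T1 is its baseline; here it is the exposure.
- The second model's list is open, and its covariates may capture some long-standing disadvantage. T1 quality of life is unnamed there, not excluded.
- If both scores measure one stable trait with equal error, the T2 coefficient falls to 1/(1 + ρ) of its value: down 23%, 33% or 41%. That is one signal split over two coefficients, and should not be read as confounding removed.
- T1 is completed after consent, within roughly two weeks of an acute admission, and the section on clinical and social measures says that psychiatric state then probably affects self-report. T1 is therefore an imperfect measure of earlier quality of life.

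What the reply does not remove is the gap between an association of the discharge level and the conditional statements about improving it. The caveat on interventions does not mention quality of life at admission.

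**Conclusion.** The point holds as a cheap improvement, not as an error in the primary analysis. The planned models estimate what Aims and objectives asks for. They cannot separate quality of life carried into hospital from quality of life reached by discharge, and the same applies to disability and empowerment.

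Bias of a given size or direction cannot be claimed. Explaining away the whole planned effect needs a T1 effect of 0.87, 0.52 or 0.37, each above 0.26. With a T1 effect of 0.13 the adjusted T2 effect is 0.24 to 0.33, little changed or larger. All of this rests on assumed correlations and the normal model above.

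A reader might also conclude that any statement about care should rest on the T1-adjusted model alone. The figures do not support that: its power can fall to between 49% and 20% when T1 and T2 are equally related to readmission, so a null T2 coefficient there would say little.

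**What to change.** Keep both planned models. Under Primary objectives, add one pre-specified sensitivity model containing the second model's covariates, the T1 EQ-5D-5L score and psychiatric status at T1, the latter for the reason the article gives about self-report at admission. Report the T1 and T2 coefficients together, with intervals. Under Secondary objectives, do the same with the T1 disability and empowerment scores; satisfaction has none.

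State in advance how the result will be used. If the T2 association does not persist, confine the Background and Discussion statements on what care should focus on to prediction. Do not read a non-significant T2 coefficient as evidence of no effect.

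Cost: three extra models and no new data. The T2 interval is wider (standard error up about 5%, 15% or 40% for assumed correlations of 0.3, 0.5 or 0.7), power is below the 75% that 430 patients give without T1, and any patient lacking a T1 score drops out of that model; the article gives no figure for how many that would be.
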